### **Role of the funders**

This is an investigator-initiated study. The management committee will take responsibility for study design and oversight. The funders will have no role in study design, data collection, management, analysis, data interpretation, manuscript writing, or in the decision to submit manuscripts for publication.

### **Coordinating centre and data management centre**

Sir Charles Gairdner Hospital acts as the co-ordinating centre and data management centre:

## 1. INTRODUCTION

### 1.1 Background and rationale

Intensive care patients can face significant health issues that extend beyond their Intensive Care Unit (ICU) stay. Despite recent advances it is estimated that one-quarter to one-half of long-stay intensive care survivors live with significant weakness as a consequence of their illness, resulting in impaired mobility and function.(1,2)

The loss of muscle mass in critical illness is related to immobility and a complicated process that causes muscle and nerve dysfunction called critical illness polymyoneuropathy. Another contributory factor is low levels of anabolic (muscle building) hormones such as testosterone – with testosterone levels in critically ill patients are extremely low, even in the recovery phase from acute illness. (3,4) One potential treatment may be to provide anabolic support in the recovery phase from prolonged critical illness.

This project aims to test whether giving a synthetic testosterone (nandrolone), will improve muscle strength in ICU survivors, when compared to placebo. Previous research has already established that early physiotherapy in the ICU can reduce length of stay and improve patients outcomes. In this study, both groups will receive standard care, which includes early physiotherapy. Nandrolone or placebo will be administered intramuscularly weekly for up to 3 weeks. Outcome measures will include hospital length of stay, time until the patient walks with assistance, muscle strength (globally and grip strength) as well as the patient's physical functioning at 3 months following enrolment.

The study design will be a double blinded randomised controlled trial, that will involve patients in WA Intensive Care Units (4 of the major units have already expressed interest in participating) and well as interstate if required.

The teams involved are multi-disciplinary, involving physiotherapy, dietitians, pharmacy as well as medical specialists. The investigators have already successfully conducted a pilot feasibility trial of a nandrolone versus placebo, showing that the intervention is safe and feasible.(5)

Given the large and increasing numbers of patients surviving intensive care both locally and internationally, (as illustrated recently with the post COVID syndrome) but with physical impairments, the results of this study would be of great interest to clinicians and patients alike.

### **Current recommendations for anabolic steroids in critical illness**

Not part of standard care.

## **1.2 Objectives**

### **Aims**

1. To reduce the time until a patient walks with one assist through the addition of an anabolic steroid (nandrolone) and resistance exercise to deconditioned ICU patients.
2. To determine whether nandrolone reduces hospital length of stay for deconditioned ICU patients.
3. To determine whether nandrolone reduces the time to return to work for deconditioned ICU patients (of working age).
4. To document changes in grip strength and limb muscle strength in the two groups in the follow-up period after enrolment.

### **HYPOTHESES:**

Nandrolone will improve muscle strength and physical functioning at hospital discharge and at follow-up 3 months after enrolment.

## **1.3 Trial design**

This study is a multicentre, parallel group, placebo-controlled, randomised, superiority trial which will allocate ICU patients in a 1:1 ratio to nandrolone in addition to standard care compared with placebo in addition to standard care.

## **2. METHODS: PARTICIPANTS, INTERVENTIONS, AND OUTCOMES**

### **2.1 Study setting**

This study will be conducted in Intensive Care Unit (ICU) and High Dependency Units (HDU) of several hospitals in Western Australia. For the purposes of this study, an HDU admission is defined as an admission of a critically unwell patient to a hospital area that includes specialised nursing at a ratio of 1:2 or 1:1.

### **2.2 Eligibility criteria**

#### **2.2.1 Inclusion criteria**

- 1.) At least 21 years of age
- 2.) Admitted to participating ICU/HDU
- 3.) Receiving nutrition at estimated goals for at least 24 hours
- 4.) ICU/HDU length of stay => 5 days

OR

Significant weakness as deemed by treating clinician below patient's baseline as a result of the ICU stay

#### **2.2.2 Exclusion criteria**

- 1.) Intercurrent septic shock (fevers, broad spectrum anti-microbials, and needing vasopressors)
2. Active cardiac disease (such as STEMI/NSTEMI in last 2 weeks) or EF <35%
3. Prostate or breast cancer
4. Ongoing reason for catabolic state (active malignancy, HIV & opportunistic infection last 2 months)

5. Unable to engage in rehabilitation (due to significant neurological or orthopaedic issues)
6. Normal age-related level of serum testosterone in males (measured in early morning 6-9am)
7. Pregnancy or breast-feeding
8. Any known allergies to nandrolone components – including peanuts and soya and latex.
9. Elevated LFTs (ALT > 5x normal) and impaired bilirubin excretion
10. Polycythaemia (Hb > 165 males, > 150 females)
11. Nephrotic syndrome.
12. Athletes competing in international/national events.
13. Expected death within the next week

## **2.3 Interventions**

### **2.3.1 Study interventions**

#### *Intervention*

Standard care (see below) with the addition of IMI nandrolone.

Dosing: Males: 100 mg weekly. Females: 50mg weekly – for 3 weeks or until hospital discharge, whichever is earlier.

The study drug will be drawn up by the ICU pharmacist, and then the syringe will be covered (to mask the contents of the syringe). All investigators, clinicians, nursing staff and patient are blinded.

NOTE: Dose change from the pilot study. The dosing was 200mg males/ 100mg females – however this is a large intramuscular volume, and can be difficult in patients without much muscle mass.

#### *Comparator group*

Will receive : standard care consists of usual physiotherapy interventions, which includes early mobilisation by staff. Early mobilisation in the ICU follows a graduated increase in activity, from passive range of motion in bed to active motion in bed to sitting/balance to assisted activity and then independent activity.

Placebo = sterile water injection or

Placebo = Normal saline (NaCl 0.9 %)

### **Concomitant therapies**

We will record

Physiotherapy received - Duration of rehabilitation physiotherapy and mobility achieved (ventilation physiotherapy treatments will not be counted).

Nutrition received - Caloric intake (kcal/total), Protein intake (g/total), Food intake (% of meals, and extrapolated calories based on meal charts from hospital).

### **Outcomes**

#### **Primary and secondary outcomes**

Primary outcome:

1. Time to walking with one person assisting (days from admission to ICU).
2. Hospital length of stay

Secondary outcomes:

1. Change in muscle strength as measured by the medical research council muscle strength (MRC) sum score - enrolment to discharge (note some ICU patients may not be able to participate in full MRC scoring, score will be extrapolated from available limbs) (9)
2. Grip strength (measured by hand held dynamometry)

3. Functional activity at hospital discharge (measured by physiotherapy staff using the Chelsea critical care physical assessment tool (CPAx (7)) and follow-up phone call at 3 months post discharge (using SF-36).
4. Hospital length of stay
5. Time to return to work (days) (for those working pre ICU).

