### **1.1 Statistical analysis and Sample size**

Trial will be prospectively registered on ANZCTR.

Efficacy of intervention will be analysed on an intention to treat basis. The analysis population is the intention to treat population defined as all study participants except for those who do not consent to use of data. There will be no imputation for missing data. A per protocol analysis will also be conducted including all participants with adherence to study medication of >80% of total study duration.

Normally and non-normally distributed data will be presented as mean and standard deviation (SD), and median and interquartile range (IQR), respectively. Between-group comparison of parametric data will be provided as mean difference and confidence interval and analysed using Student's t test. Between-group comparison of non-parametric data will be presented at median difference and analysed using the Mann-Whitney U test. For dichotomous data, frequencies and percentages will be presented and between-group analysis will use Fischer's Exact or Chi-squared test as appropriate. The numbers at risk in each group and the number and proportion of events observed will be reported, as well as the equivalent absolute risk difference, relative risk ratio and corresponding 95% confidence intervals. Survival time from randomisation until day 60, according to treatment group will be displayed as Kaplan-Meier curves and analysed using a log-rank test. Estimates of hazard ratios for survival, with corresponding 95% CI and P values, will be obtained from the Cox proportional hazards models incorporating treatment group alone, and independent covariates used in the multivariate models. Secondary analysis will also be conducted adjusting the primary outcome variable for prespecified baseline covariates (age, gender, APACHE-II score, BMI) in a transformed multivariable linear regression model including

baseline univariate variables with a  $p < 0.05$ . For all outcome analyses a two-sided P value of  $< 0.05$  will be considered significant.

Baseline variables recorded to demonstrate that the groups are comparable; if this is not demonstrated, *post-hoc* adjustments to correct for differences will be applied.

Sample size calculation: 60.

This is based on several different assumptions and outcome measures:

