1. Hospital length of stay, as sample of  $n=24$  per group has 80% power to detect a median difference of 3 days LOS (26 vs 23 days) with IQR 5.4 between independent groups (this is a conservative estimate as in the pilot, LOS results were 26 vs 36 days).
2. Time to walking with one-assist (ICU mobility scale). A sample of 24 per group has 80% power to detect a difference in proportions of 40 between the intervention and control groups, of patients walking with one assist at discharge (from a baseline of 27% in pilot).

To allow for loss to follow-up, the sample size number increased to 60.

Subgroup analysis: due to potential heterogeneity in patients, stratification based on MRC score,  $\geq 48$  (48 is an accepted cut off for ICU acquired weakness).

Economic evaluation:

An economic evaluation will be performed. Cost offsets from any reduction in LoS will be estimated separately for ICU stay and total hospital stay, and costed using hospital-specific per day costs. We will estimate QALYs using the SF-36 data converted to SF-6D using Australian population weights.(6)

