### **Allocation concealment**

Allocation concealment will be maintained by using sealed, sequentially numbered, opaque envelopes at each study site containing the study number corresponding to the allocated study number. Randomisation will not be performed until participants fulfil all eligibility criteria and are ready to be assigned to study treatment.

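### Time to walking is counted from ICU admission, so primary outcome 1 includes pre-randomisation days, and possibly walking events, that the drug cannot affect

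*Protocol*

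**What the plan says.** The first aim is "To reduce the time until a patient walks with one assist". Under Primary and secondary outcomes, the first primary outcome is "Time to walking with one person assisting (days from admission to ICU", so day zero is ICU admission.

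Section 2.2.1 admits a patient with "ICU/HDU length of stay => 5 days" or, as an alternative, "Significant weakness as deemed by treating clinician below patient's baseline as a result of the ICU stay". The stay alone is sufficient. Among the exclusions in section 2.2.2, the only one about mobility works in the other direction: "Unable to engage in rehabilitation (due to significant neurological or orthopaedic issues". Under Allocation concealment, "Randomisation will not be performed until participants fulfil all eligibility criteria and are ready to be assigned to study treatment".

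Elsewhere the protocol uses a different origin. Section 1.1 on statistical analysis analyses "Survival time from randomisation until day 60". The prespecified adjustment covariates there are age, gender, APACHE-II score and BMI. Time from ICU admission to randomisation is not among them.

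Hospital length of stay is the second primary outcome and has no stated origin.

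**The concern.** A treatment can change only what happens after it is assigned. Two features of the outcome as written conflict with that.

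- **Pre-treatment days.** Every patient on the length-of-stay route carries at least 5 days in the ICU or HDU before randomisation, with no upper limit. Those on the weakness route may be randomised sooner. The interval therefore differs between patients, and its spread goes into the outcome.
- **Pre-treatment events.** A patient who already walks with one assist at randomisation has an outcome value that was settled before the first injection. The protocol does not say how such a patient is counted.

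With 60 patients, precision is scarce. The first feature adds variance unrelated to treatment. The second mixes in patients whose treatment effect on this outcome must be zero.

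**Working it through.** **1. The plan's own walking calculation.** Section 1.1 powers walking on the proportion walking with one assist at discharge: 27% in controls plus 40 points, so 27% against 67%, with 80% power and 24 per group. With a two-sided 5% level and pooled variance (mean proportion 0.47):

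n = [1.960·√(2·0.47·0.53) + 0.842·√(0.27·0.73 + 0.67·0.33)]² / 0.40² = (1.383 + 0.544)² / 0.16 ≈ 23.2, rounded up to 24.

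The figure reproduces, with power 81.4% at 24 per group. It concerns a proportion at discharge and does not depend on where day zero lies. It therefore says nothing about the precision of the time outcome.

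**2. What the outcome contains.** Write T = D + R, where D is days from ICU admission to randomisation and R is days from randomisation to first walking with one assist. On the length-of-stay route D is at least 5. Treatment acts on R only. For a patient already walking at randomisation, T is shorter than D and treatment has no part in it.

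**3. Could patients already be walking?** Nothing in sections 2.2.1 and 2.2.2 rules it out. Under Comparator group, standard care includes early mobilisation that progresses to assisted and then independent activity. The planned "stratification based on MRC score" at 48, described as the cut-off for ICU-acquired weakness, implies that patients without such weakness are expected. The aims speak of deconditioned patients, but that is not an entry criterion.

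**4. Cost of the added variance (illustration).** The protocol gives no SD for R or for D. Assumptions: effect 3 days; SD of R 4 days; 30 per group; two-sided t test at 5%; D and R uncorrelated. The 3 days and the 4 days are borrowed as a scale from the length-of-stay line (23 against 26 days, IQR 5.4; 5.4/1.349 = 4.0).

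SD(T) = √(4² + s²), where s is the SD of D; standardised effect d = 3/SD(T).

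| s (days) | SD(T) | d | Power |
|---|---|---|---|
| 0 (counted from randomisation) | 4.00 | 0.75 | about 81% |
| 2 | 4.47 | 0.67 | 72% |
| 3 | 5.00 | 0.60 | 63% |
| 4 | 5.66 | 0.53 | 52% |

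**5. Sensitivity to correlation.** With correlation r between D and R, SD(T) = √(16 + s² + 8rs). For s = 2, 3 and 4:

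- r = +0.3: power 63%, 52% and 43%.
- r = −0.3: power 83%, 77% and 68%, so there is no loss at s = 2.

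**The case against.** The strongest reply is that the table is not an estimate for this trial, and that is right. The 3 days and SD of 4 come from a hospital length-of-stay assumption. If 26 and 23 days are whole stays, the IQR of 5.4 already includes pre-randomisation days. On that reading power is about 81% as the plan stands, and removing an uncorrelated delay with SD 2 would leave √(16 − 4) = 3.46 days and raise power to 91%. The level shifts, but the direction does not. A t test on days is also a simplification: if only 27% of controls walk with one assist by discharge, most have no walking time by then.

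A reader might also infer more than the documents support.

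- **Bias between arms.** Delay and prior walking are fixed before allocation, so randomisation balances them in expectation.
- **Immortal time.** The Kaplan-Meier, log-rank and Cox analyses in section 1.1 are described for survival, which already starts at randomisation. No hazard analysis of walking is stated.
- **A percentage for the power lost to patients already walking.** Their share is not given. The pilot's 27% walking at discharge suggests that it is modest, and that 27% would already include any such patients, so adding them again counts them twice.
- **A need to exclude them from the trial.** They still inform strength, SF-36, return to work and length of stay. A narrower entry rule would cost recruitment by an amount that cannot be judged from the protocol.
- **The same defect in length of stay.** No origin is stated, so the point is conditional there. Total stay also has a stated use in the economic evaluation.

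What stands against all this is the explicit origin of primary outcome 1, the timing of randomisation, and the absence of any rule for patients already walking.

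**Conclusion.** The point holds as a weakness in a stated rule, and not as a detail left to a later document. Primary outcome 1 includes time before treatment for every patient, at least 5 days on the length-of-stay route, and may include events before treatment. The consequence is lost precision and dilution, not bias.

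The size is unknown. The fall from about 81% to 72-52% rests on an assumed 3-day effect, an assumed post-randomisation SD of 4 days, an assumed delay SD of 2-4 days and zero correlation. A negative correlation between delay and later recovery could remove the loss at the low end of that range, and a positive one would enlarge it. The planned 24 per group for the proportion walking at discharge is unaffected by the time origin. The change is worth making because it is cheap and the trial is small.

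**What to change.** - Define primary outcome 1 as days from randomisation to first walking with one assist, the same origin as for survival. Keep days from ICU admission as a descriptive measure.
- Prespecify days from ICU admission to randomisation as a baseline covariate. In an untransformed linear model with this covariate the treatment estimate is the same from either origin, since T and R differ only by D.
- Record mobility level at randomisation. Prespecify that walking time is compared in patients not yet walking with one assist at that point. The subset is defined before treatment, so the comparison stays randomised. Keep all patients in the other outcomes.
- State the origin of length of stay. If it is hospital admission, use the same covariate in the treatment comparison, or count from randomisation. Keep total stay for the economic evaluation.

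The cost is amendment wording and some data capture. The Data Collection list mentions mobility achieved but names no randomisation date, first-walk date or mobility level at enrolment. The survival analysis already needs the first and the current outcome the second, so the baseline mobility level is the real addition. A few patients may leave the walking-time comparison.

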## **1.2 Data management**

Study data will be entered directly into a secure web-based case report form with the option to print blank and completed forms. A detailed study monitoring plan will be prepared by the study management committee prior to commencement of the study. On site source monitoring will be conducted by the co-ordinating centre and will include 100% source data verification for the primary end point. Source data verification will be completed for all data points for the first two patients at each centre and for a random sample of patients during monitoring visits thereafter.

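### Hospital length of stay is listed as both primary and secondary, two primaries are each tested at 5%, and no rule says which result makes the trial positive

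*Protocol*

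**What the plan says.** All places are in the protocol.

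- **Outcomes, Primary and secondary outcomes.** The primary heading carries two numbered items: "Time to walking with one person assisting (days from admission to ICU") and "Hospital length of stay". The secondary list repeats length of stay as item 4, in the same words.
- **Section 1.1, significance level.** "For all outcome analyses a two-sided P value of" less than 0.05 is the threshold. No alpha split, hierarchy or adjustment is given.
- **Section 1.1, adjusted analysis.** The regression is described as "adjusting the primary outcome variable for prespecified baseline covariates", in the singular.
- **Section 1.2 Data management.** Monitoring includes "100% source data verification for the primary end point", again in the singular.
- **Section 1.1, sample size.** The total of 60 is introduced with "This is based on several different assumptions and outcome measures". Length of stay and walking then each receive their own 24 per group at 80% power, with length of stay first.
- **Section 1.2 Objectives, Aims.** Time to walking is Aim 1. Aim 2 is "To determine whether nandrolone reduces hospital length of stay for deconditioned ICU patients".
- **Hypotheses.** "Nandrolone will improve muscle strength and physical functioning at hospital discharge and at follow-up 3 months after enrolment". Neither primary outcome is named.

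**The concern.** A primary outcome defines what counts as a positive trial. Here one endpoint carries both labels, and two parts of the text assume a single primary without saying which. If walking and length of stay disagree at the end, the protocol gives no means of deciding whether the trial succeeded.

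There are two separate defects:

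1. **The double listing.** Length of stay cannot be both primary and secondary. This leaves its status open, but does not by itself change any error rate.
2. **Two unadjusted tests without a decision rule.** If a significant result on either outcome is taken as success, the false-positive rate for the primary claim exceeds the nominal 5%.

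This goes beyond detail that could wait for a statistical analysis plan. The protocol itself names the primary outcomes inconsistently and fixes p<0.05 for every outcome. A later plan would have to choose between the two lists, and could add a multiplicity adjustment only by departing from that threshold.

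**Working it through.** **Inputs.** From the protocol: two primary outcomes; two-sided alpha 0.05 for each; no planned interim analysis; 24 per group for each outcome, raised to 60 in total for loss to follow-up; length of stay 26 vs 23 days with IQR 5.4; walking with one assist at discharge from a 27% baseline with a difference of 40, read as percentage points (27% vs 67%). Assumed: SD = IQR/1.349 = 5.4/1.349 = 4.00 days, which holds under normality. The protocol gives no correlation between the outcomes, so a range is shown.

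**Step 1: the plan's own sample sizes.**

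- Walking, two-sided 0.05, 80% power, 27% vs 67%, no continuity correction: 24 per group (power at 24 is 81.4%). This reproduces.
- Length of stay: n = 2(1.96 + 0.84)² × (4.00/3)² ≈ 28 per group. The stated 24 does not reproduce with a two-sided test; power at 24 is 72.0% by the noncentral t. One-sided 0.05 gives 23, close to 24, but the protocol says two-sided.
- Each calculation treats its outcome alone, at full alpha.

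**Step 2: error rate if either outcome suffices.**

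- Independent outcomes: 1 − (1 − 0.05)² = 1 − 0.9025 = 0.0975.
- Correlated outcomes: 1 − P(|Z1| < 1.96 and |Z2| < 1.96), with Z1 and Z2 bivariate normal.

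| Correlation | Chance of at least one false positive |
|---|---|
| 0 | 9.75% |
| 0.3 | 9.5% |
| 0.5 | 9.1% |
| 0.7 | 8.3% |
| 0.8 | 7.8% |
| 0.9 | 7.0% |

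**Step 3: error rate under the other readings.**

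- Both required: a false claim needs a false rejection of at least one true null hypothesis at 0.05, so the rate is at most 5%.
- Length of stay meant only as secondary: one primary test, 5%.

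**Step 4: power under each repair.** The worst case under Holm is that an outcome must be tested at 0.05/2 = 0.025. Length of stay uses the noncentral t with difference 3 and SD 4.00. Walking uses the two-proportion normal approximation.

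| Outcome | Per group | Power at 0.05 | Power at 0.025 |
|---|---|---|---|
| Length of stay | 24 | 72% | 61% |
| Length of stay | 30 | 81% | 73% |
| Walking at discharge | 24 | 81% | 72% |
| Walking at discharge | 30 | 89% | 83% |

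If both must be significant, joint power at 24 per group would be about 0.720 × 0.814 = 0.586, or 59%, if the outcomes were independent. It would be higher under positive correlation, but cannot exceed the 72% for length of stay.

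**The case against.** **The inflation is conditional.** A reader might infer that the trial simply has a 9% to 10% false-positive rate. The documents do not support that. They never say that either outcome suffices, and the singular wording in sections 1.1 and 1.2 fits one intended primary. Late walking and long stay are also plausibly well correlated, which pulls the figure towards 7% to 8%. This objection stands against an unconditional figure. It does not remove the defect, because the protocol does not state which rule applies.

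**The double listing does not cause the inflation.** This is correct. The inflation comes from two unadjusted tests, and the repeated entry is a contradiction in its own right. That length of stay might be relabelled once results are known is a possibility the wording leaves open, not something the protocol shows to be intended. The protocol promises prospective registration, and the registry record, which is not at hand, might settle the designation.

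**Walking is not the obvious sole primary.** It is Aim 1 and is listed first among the outcomes, so a reader might infer that it should stand alone. But the sample-size list puts length of stay first, and what is powered for walking is the proportion walking with one assist at discharge, not the time to walking named as the outcome. The documents do not settle the choice.

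**The hypothesis.** It names neither primary outcome, but physical functioning at discharge could reasonably include walking with assistance, and Aims 1 and 2 name both primaries. This is loose wording to be aligned, not a further error.

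**Multiplicity rules often sit in the analysis plan.** True in general, but this protocol already fixes the unadjusted threshold and the conflicting labels.

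**Conclusion.** The point holds as a contradiction with an undefined success rule. Length of stay has two incompatible labels, two primaries are tested at 0.05 each, and nothing says whether one or both must succeed. The false-positive rate for a primary claim is up to 9.75% if either outcome counts (about 7% to 9.75% for correlations from 0.9 to 0), and at most 5% if both are required. These figures assume two-sided tests at 0.05 with jointly normal test statistics; the correlation is an assumption. Whatever the exact rate, the primary criterion should be settled before unblinding, because in a trial of 60 it carries the main claim.

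**What to change.** List length of stay once only, and fix one success rule by protocol amendment before unblinding. Either route is adequate:

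- **(a) One sole primary outcome**, with the other as first key secondary, tested at 0.05 only if the primary is significant. No alpha is split.
- **(b) Both remain primary.** Delete secondary outcome 4, and either apply Holm at an overall 5% or state that both must be significant at 0.05.

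The investigators should choose. The hypothesis, the adjusted-analysis wording in section 1.1 and the source-verification wording in section 1.2 should then be aligned with that choice. If walking is chosen, the endpoint (time to walking) must be reconciled with the quantity powered (proportion walking at discharge).

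**Cost.** Mainly amendment wording. Under (a), one outcome stops being an independent route to a positive claim. Under Holm, length-of-stay power in the worst case falls from about 72% to 61% at 24 evaluable per group, or from 81% to 73% if all 30 per group are evaluable (SD 4.0 assumed). It would be too optimistic to quote only the figures for 30, since the protocol plans on 24 and adds the rest for losses. A both-required rule avoids splitting alpha but lowers the joint power, as shown in the working.

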## **Consent**

The majority of patients enrolled in this trial will have capacity to give consent at the time of trial enrolment. The following consent options are acceptable: (i) consent by the patient (ii) consent by a substitute decision maker using the IMP / GAA pathway for WA Health; (iii) Delayed consent from the patient. All participants who recover sufficiently will be given the opportunity to provide informed consent for ongoing study participation and for the use of data collected for the study.

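### Patients with no testable limb at enrolment drop out of the MRC strength comparison even when they are scored at discharge, because the outcome is a raw change with no imputation

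*Protocol*

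**What the plan says.** All references are to the Protocol.

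- **Outcome.** Under Primary and secondary outcomes, the first secondary outcome is "Change in muscle strength as measured by the medical research council muscle strength (MRC) sum score - enrolment to discharge". It needs a score at both times. A note to it reads "note some ICU patients may not be able to participate in full MRC scoring, score will be extrapolated from available limbs".
- **Grip.** The next secondary outcome is "Grip strength (measured by hand held dynamometry"), with no reference to change and no time point. Only the fourth aim mentions change: "To document changes in grip strength and limb muscle strength in the two groups in the follow-up period after enrolment".
- **Analysis.** Section 1.1, Statistical analysis and Sample size, compares continuous outcomes by Student's t test or Mann-Whitney U. It says "There will be no imputation for missing data", without restriction. It also says "The analysis population is the intention to treat population defined as all study participants except for those who do not consent to use of data".
- **Who can be enrolled.** The Consent section says "The majority of patients enrolled in this trial will have capacity to give consent at the time of trial enrolment" and accepts consent by a substitute decision maker and delayed consent. The only exclusion based on ability to take part is "Unable to engage in rehabilitation (due to significant neurological or orthopaedic issues") (section 2.2.2). No inclusion criterion asks for wakefulness or cooperation.
- **Schedule.** MRC and grip are measured weekly (Data collection methods).

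**The concern.** The hypothesis names muscle strength at hospital discharge. A change score makes the discharge value usable only when an enrolment value exists. MRC testing needs a patient who can respond to the tester, and the enrolment rules leave room for some who cannot. For them the protocol collects a valid discharge score and then cannot use it. That sits badly with an analysis population meant to hold everyone who agrees to use of their data.

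In a trial of 60 patients, each discarded score costs precision. It also limits the strength result to patients who could already be tested at entry. The MRC-48 subgroup would lose the same patients if it is defined on the enrolment score; the protocol does not say which score it uses.

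**Working it through.** **Step 1: follow one patient through the text.** Take a patient enrolled without capacity for a reason that is neither neurological nor orthopaedic, with no limb testable at enrolment, who recovers and is fully scored at discharge.

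1. Eligible: no inclusion criterion or exclusion stops this patient.
2. Enrolment MRC: none. Extrapolation needs at least one tested limb.
3. Change score: discharge minus enrolment, undefined.
4. Imputation: ruled out.
5. t test or Mann-Whitney U on change: the patient is absent, although in the intention-to-treat population.

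Weekly MRC does not repair this. A first score taken after dosing has begun is not a baseline, and using it as one could absorb part of any treatment effect.

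**Step 2: the plan's own figures.** There is no effect, SD or sample size for MRC to reproduce. The total of 60 (30 per arm) comes from other outcomes. For walking with one assist, 27% against 67%, two-sided 5% and 80% power, the stated 24 per group does reproduce; 48/(1 − 0.20) = 60 implies a 20% allowance for loss. The present point depends on none of these.

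**Step 3: illustrative loss of power.** Assumptions: a share f has no enrolment score (10% to 40%; the protocol gives no figure), everyone else has both scores, and full data from 30 per arm would give 80% power. For a two-sided 5% t test that means a standardised effect d = 0.736. The analysed number per arm is 30(1 − f), and the detectable difference grows by 1/√(1 − f).

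| f | Analysed per arm (total) | Power | Detectable difference |
|---|---|---|---|
| 0 | 30 (60) | 80% | × 1.00 |
| 10% | 27 (54) | 75.6% | × 1.05 |
| 20% | 24 (48) | 70.4% | × 1.12 |
| 30% | 21 (42) | 64.3% | × 1.20 |
| 40% | 18 (36) | 57.3% | × 1.29 |

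The normal approximation (d = 0.723) gives 75.7%, 70.7%, 65.0% and 58.3%.

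**Step 4: what the remedy recovers.** Take equal variances (set to 1) at enrolment and discharge, correlation r, and f = 0.2. Information relative to an unadjusted comparison of discharge scores in all patients is:

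- change, complete cases: (1 − f)/[2(1 − r)]
- adjusted regression, complete cases: (1 − f)/(1 − r²)
- adjusted regression, baseline filled in, all patients weighted equally: 1/[(1 − f)(1 − r²) + f]
- the same with separate residual variances, treated as known: (1 − f)/(1 − r²) + f

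| r | Change | Adjusted, complete cases | Filled in, equal weights | Filled in, separate variances |
|---|---|---|---|---|
| 0.5 | 0.80 | 1.07 | 1.25 | 1.27 |
| 0.7 | 1.33 | 1.57 | 1.64 | 1.77 |
| 0.8 | 2.00 | 2.22 | 2.05 | 2.42 |

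Example, r = 0.7, equal weights: 0.8 × 0.51 + 0.2 = 0.608, and 1/0.608 = 1.64.

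Replacing change by adjustment helps in every row. Filling in adds a further gain at r = 0.5 and a small one at r = 0.7. At r = 0.8 with equal weights it is below the complete-case adjusted analysis (2.05 against 2.22), because the filled-in patients carry the full unadjusted variance. With separate variances they still add a little.

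**The case against.** Several counter-arguments have force.

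- **Lack of capacity is not inability to be tested.** A reader might infer that every patient enrolled without capacity is lost. The documents do not say so. A confused patient may lack capacity to consent and still move one limb on request, and one limb is enough for extrapolation. The affected group is a subset of a minority and may be small. This stands.
- **Grip.** A reader might extend the point to grip strength. The outcome list does not define grip as a change, and the fourth aim only speaks of documenting changes. A missing enrolment grip value does not by itself remove a discharge value. This stands.
- **Bias.** A reader might infer a biased treatment comparison. If the enrolment score precedes treatment, its absence should not depend on arm. No such bias is shown.
- **Importance.** The outcome is one of five secondary outcomes and the trial is not powered on it. Nothing in the text says the drug is aimed at patients who cannot cooperate. This stands.
- **Size.** Both the 10% to 40% range and the 80% reference are assumed, and the illustration starts from discharge scores in all 60. This stands.
- **It belongs in the SAP.** Covariate adjustment and missing baselines are often left to a SAP, which may exist. This stands only in part: the protocol itself fixes a change outcome, names unadjusted tests and bars imputation without limit, so a SAP that filled in baselines would contradict it.

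**Conclusion.** The point holds in a limited form. Patients with no testable limb at enrolment leave the MRC comparison despite a discharge score, and neither limb extrapolation nor weekly measurement brings them back. The consequence is lower precision and a narrower analysed population on one unpowered secondary outcome.

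The number affected cannot be derived from the protocol. The fall from 80% to between about 76% and 57% power holds only under the assumed shares and the assumed reference power. The case for change does not rest on those figures: enrolment MRC is already collected, and in the calculation above adjusting for it is more precise than the raw change even in complete cases.

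**What to change.** 1. Under Primary and secondary outcomes, define the outcome as the MRC sum score at hospital discharge. In section 1.1, analyse it by regression on arm with enrolment MRC as a covariate.
2. In section 1.1, limit the ban on imputation to outcomes, and reconcile it with the note on extrapolating from tested limbs.
3. Where enrolment MRC could not be tested, set the covariate to the mean over both arms combined and add a not-testable indicator, so that every patient with a discharge score is analysed. Because these values precede treatment, filling them in does not favour either arm.
4. Allow for the larger residual variance in those patients. Robust standard errors make the inference valid; separate variances also avoid the precision loss seen at r = 0.8.
5. Report the complete-case adjusted analysis as a sensitivity analysis.

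**Cost.** Protocol or SAP wording and one eCRF tick box for not testable at enrolment; no extra visits or patients. The downside is little or no precision gain from the filled-in patients when the enrolment-discharge correlation is very high. The benefit is then mainly the broader analysed population.
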